### Data collection and management

#### Overview

Figure 1 outlines the study design and assessments, and Fig. 2 (SPIRIT figure) summarises assessment timing. Assessments will be conducted remotely (over the phone or via MS Teams) unless a face-to-face meeting is strongly preferred by the participant. The researcher will enter participant responses to study measures into an electronic case report form (e-CRF) via the web-based Qualtrics survey system. Participants will be reimbursed with £20 shopping voucher for each study assessment session they participate in.

**Fig. 2 Fig2:**
[figure not shown]
SPIRIT figure. ^***a***^If a participant scores above the screening threshold (via digital screening or usual care), blinded PHQ-9 and GAD-7 assessments will be completed to confirm whether it is a true positive screen. PHQ-9 = Patient Health Questionnaire; GAD-7 = Generalised Anxiety Disorder questionnaire; MINI = Mini International Neuropsychiatric Interview; PBQ = Postpartum Bonding Questionnaire; HRUQ = Healthcare Resource Use Questionnaire; Abridged MARS = Mobile App Rating Scale

#### Baseline assessment (both groups)

At baseline, a research assistant or research midwife will assess participants using three self-report measures: a 9-item measure of depression (PHQ-9, Patient Health Questionnaire) [30], a 7-item measure of anxiety (GAD-7, Generalised Anxiety Disorder questionnaire) [31] and a generic health status measure (EQ-5D-5L) [34]. Demographic information will be collected with a questionnaire assessing age, gender, ethnicity, employment status, family composition, native language and past psychiatric history.

#### Case note review (baseline until 8 weeks postpartum; both groups)

An unblinded researcher will review all participant electronic health records (midwife, GP, and health visitor case notes) on a weekly basis from baseline until 8 weeks postpartum and extract all reported EPDS scores (total score and individual item scores). Participants scoring above the standard care EPDS threshold (total EPDS ≥ 12) will be counted as a positive screen. Positive screens will be referred to a blinded researcher for assessment with PHQ-9/GAD-7 within 48 h. Participants scoring above threshold on the PHQ-9 (total score ≥ 10) [30] or GAD-7 (total score ≥ 10) [31] will be counted as true positives. Participants scoring below PHQ-9 and GAD-7 thresholds will be counted as false positives.

Additional cross-sectional information will be collected from electronic health records for all participants: answers to mental health screening questions and past psychiatric history reported at booking appointment, details of current childbirth (mode of delivery, live/still birth, any major obstetric complications), parity (total number of pregnancies reaching viable gestational age).

#### Blinded follow up assessments: 8 weeks and 6 months postpartum (both groups)

At 8 weeks and 6 months postpartum, a blinded researcher will assess all participants using the MINI, a short, structured diagnostic interview for DSM-IV and ICD- 10 psychiatric diagnoses [35]. Three relevant subscales of the MINI will be used in this study: major depression (subscale A), suicidality (subscale B) and generalised anxiety disorder (subscale N). Participants will also be assessed with three self-report measures during each follow-up assessment: a generic health status questionnaire (EQ-5D-5L), a bespoke questionnaire assessing health and social care resource use during the follow up period (unpublished), and a validated questionnaire assessing parental bonding with their baby (Postpartum Bonding Questionnaire) [36]. Regarding choice of assessment timepoints, the 8-week postpartum assessment aligns with the end of the intervention period. The 6-month postpartum assessment point was chosen to allow time for screening (digital screening or usual care screening) to have an effect on participants’ mental health. Specifically, time will be needed for participants screening positive for PND to be referred for additional mental health care (e.g. talking therapy, medication) and for that care to take effect.

#### App feedback: 8 weeks postpartum (unblinded assessment; digital screening group only)

An unblinded assessment will be conducted at 8 weeks postpartum to gather feedback about the study smartphone app. All participants from the digital screening group will be asked to give feedback on the app using the Abridged Mobile App Rating Scale (MARS), a 12-item questionnaire assessing acceptability and usability of health-related smartphone apps [37]. A sub-group of up to 30 participants from the digital screening group will be invited to take part in a semi-structured qualitative interview exploring the acceptability of digital screening and study procedures, and implementation barriers/facilitators. Participants will be purposively sampled to include individuals with a range of demographic characteristics and app-use levels (including app discontinuers). This will ensure that a variety of views are gathered regarding the acceptability of the app-based screening. Interviews will follow a topic guide (Supplementary material 1), last 30–60 min and be audio recorded using an encrypted device and later transcribed verbatim. Separate consent will be sought for qualitative interviews to be sure that participants fully agree to participate.

#### Data protection and confidentiality

Study data will be pseudonymised. All participants will be allocated a unique study ID number. Participant names and other identifying information will be removed from study data and interview transcripts, which will then be identified by the study ID number only. Personal identifiable data (name, address, audio-recordings, etc.) will be securely stored separately from pseudonymised study data. Confidentiality of information provided during the research will only be broken if a participant is assessed to be at risk to themselves or others (or discloses significant bad practice); participants will be informed of this procedure prior to giving consent.

### Data analysis

Analysis will be on an intention-to-treat basis, with participant data analysed according to the arm to which they were randomly allocated. Protocol deviations will be noted, and their frequency used to inform the power calculation for the larger study (c.f. contamination). A protocol deviation is defined by the study sponsor as “an action or incident inconsistent with the original, approved protocol that is documented after it occurs”. A CONSORT diagram will present information on the number of potential participants identified, number eligible/ineligible (with reasons for ineligibility), number declining to participate (with reasons, where reported), as well as information on the number of actual participants consented, baseline assessed, randomised, and retained in the study at both 8 weeks and 6 months postpartum. Additionally, the CONSORT diagram will detail the number of participants receiving the treatment to which they were randomised, withdrawals from the digital screening intervention arm (with reasons) and number of withdrawals/dropouts from the trial (by trial arm, with reasons).

#### Primary outcome

The key measures of feasibility will be reported using descriptive statistics:i.App engagement: overall percentage of app-based assessments completed during the app-use period; percentage of participants completing > 50% app-based assessments.ii.Retention: percentage of participants retained at 8 weeks postpartum; percentage of participants retained at 6 months postpartum.iii.Data completeness: the extent and pattern of missing data from participant electronic health records (midwife, GP and health visitor records from baseline to 8 weeks postpartum) and MINI at 6 months postpartum.

#### Secondary outcomes

Appropriate descriptive statistics will be used to summarise: baseline participant socio-demographic data (by trial arm), the extent and pattern of missing data for clinical outcomes (PHQ-9, GAD-7, MINI, Postpartum Bonding Questionnaire) and health economics outcomes (Healthcare Resource Use Questionnaire, EQ-5D-5L) at each time point, questionnaire completion rates (i.e. the number of individual items completed), variability in the responses across participants and floor/ceiling effects, and the number and type of Adverse Events (by trial arm).

Data on the acceptability and usage of ClinTouch PND app will be analysed for the digital screening group only. Total and item scores on the MARS questionnaire will be summarised descriptively (median and range). Qualitative interviews with those selected in the app group will be analysed using framework analysis [38], with analysis managed using Nvivo software [39]. Framework analysis is a systematic qualitative research method which follows a structured approach, enabling researchers to identify key themes while maintaining transparency and rigor [38]. Its matrix-based structure facilitates comparison across cases and themes, ensuring coherence and depth in qualitative inquiry. The process involves several stages: familiarisation with the data, developing a thematic framework, indexing (systematically coding all transcripts), charting (creating the framework matrix table), and mapping and interpreting the data. Unlike purely inductive qualitative methods, framework analysis allows for both deductive and inductive coding [38], making it adaptable for studies wishing to explore predefined questions (e.g. “Is the frequency of digital screening (daily) suitable?”) as well as exploring unanticipated aspects of the qualitative data.

#### Tertiary outcomes

Summary statistics will be reported for each clinical outcome measure and health economics measure, by group, at each time point. As this is a feasibility study, no formal statistical tests comparing treatment groups will be conducted. No model-based imputation (e.g. multiple imputation) of missing data items will be attempted; missing data items will assume the mean value of all completed items on that measure for a particular individual (assuming that sufficient items have been completed). Health utility values will be estimated using the method recommended by NICE at the time of the analysis. Mean utility values will be reported at each time point and quality-adjusted life years (QALYs) estimated across the whole study period. These will be reported by treatment allocation group. Responses on the EQ-5D-5L will be compared with results from key clinical outcome measures to determine whether the characteristics (e.g. direction) of any observed health effects are comparable according to the different measures. The number and proportion of participants reporting use of different health and social care services (and quantity of services used) will be summarised by treatment allocation group.

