#### Tertiary outcomes

Summary statistics for the two candidate primary outcomes for a full-scale trial:The number of true positive and false positive screens identified by usual care and digital screening between baseline and 8 weeks postpartum. True positives are defined as cases scoring above EPDS screening threshold (usual care threshold: total EPDS score ≥ 12; digital screening threshold: total EPDS ≥ 12 on three consecutive reports) and scoring ≥ 10 on PHQ-9 or GAD-7 in a subsequent assessment by a blinded researcher. False positives are cases scoring above EPDS screening threshold but scoring < 10 on PHQ-9 and GAD-7.MINI score at 6 months postpartum.Summary statistics for the other clinical outcomes (MINI, Postpartum Bonding Questionnaire) and health economic outcomes (Healthcare Resource Use Questionnaire, EQ-5D-5L) at 8 weeks postpartum and 6 months postpartum.Key drivers of cost identified by the Healthcare Resource Use Questionnaire.

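### The single missing-item rule (person-mean of completed items) is written without exemption and so reaches EQ-5D-5L, the resource-use questionnaire and the MINI, which it does not suit

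*Protocol article*

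**What the plan says.** The rule stands in the protocol article under Data analysis, Tertiary outcomes. The paragraph opens with its scope: "Summary statistics will be reported for each clinical outcome measure and health economics measure, by group, at each time point". It then excludes one approach, "No model-based imputation (e.g. multiple imputation) of missing data items will be attempted", and adopts another: "missing data items will assume the mean value of all completed items on that measure for a particular individual". A condition follows in brackets, "assuming that sufficient items have been completed", without a number.

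The same paragraph goes on to the health economic outputs. On valuation it says "Health utility values will be estimated using the method recommended by NICE at the time of the analysis". On use it says "Mean utility values will be reported at each time point and quality-adjusted life years (QALYs) estimated across the whole study period". On resource use it says "The number and proportion of participants reporting use of different health and social care services (and quantity of services used) will be summarised", by allocation group.

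The measures in scope are listed under Outcomes, Tertiary outcomes: "Summary statistics for the other clinical outcomes (MINI, Postpartum Bonding Questionnaire) and health economic outcomes (Healthcare Resource Use Questionnaire, EQ-5D-5L"), at both follow-ups. That list also includes the 6-month MINI, as a candidate primary outcome for the full trial, and the main cost drivers. The section on blinded follow-up assessments describes the MINI as a structured diagnostic interview from which three modules are used: depression, suicidality and generalised anxiety.

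**The concern.** Replacing a missing item by the person's own mean is a reasonable prorating device when items are alike and are added into a score, as with PHQ-9, GAD-7 and the Postpartum Bonding Questionnaire. It depends on any item being a fair stand-in for any other.

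That does not hold for the other three measures. EQ-5D-5L dimensions are separate aspects of health, valued together as a profile of whole levels. Resource-use items count different services. MINI answers feed a diagnostic algorithm, and the measure spans three conditions.

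At stake are the descriptive summaries meant to help plan the full trial: mean utilities, QALYs, service users and quantities, cost drivers and MINI summaries. The Objectives section makes the suitability of these measures a secondary objective, so values filled in by an unsuitable rule would weaken that assessment.

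**Working it through.** The plan states no figure for this point, so there is none to reproduce. The check takes the rule literally, measure by measure. The item structures, response distributions and counts below are assumptions, because the article does not give them.

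**1. Scope.** The opening sentence of the paragraph covers every clinical and health economic measure. The rule refers to whichever measure has the gap and exempts none. The outcome list places the MINI, the bonding questionnaire, the resource-use questionnaire and EQ-5D-5L within it. Three of these four are not summed scales.

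**2. EQ-5D-5L** (assumed: five items, levels 1 to 5).
- Single case: answers 1, 1, 1, 3 and one missing. Imputed level = (1 + 1 + 1 + 3)/4 = 6/4 = 1.5, which is not a level.
- General case: with k items completed, the imputed value is a whole level only if their sum is divisible by k. For k = 4 there are 5^4 = 625 patterns; 157 have a sum divisible by 4 and 468 do not. 468/625 = 74.9%.
- Weighting the patterns by assumed level probabilities, with items independent:

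| Level probabilities (1 to 5) | One item missing: not a whole level | Two items missing: not a whole level |
|---|---|---|
| 0.20 each | 74.9% | 67.2% |
| 0.60, 0.25, 0.10, 0.04, 0.01 | 74.2% | 61.9% |
| 0.80, 0.15, 0.04, 0.01, 0 | 56.4% | 43.6% |

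Dimensions that move together would probably lower these shares. In the remaining 25.1% to 43.6% of one-item cases the result is a scoreable level, but one borrowed from the other four dimensions.

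**3. Resource use** (assumed counts for four services: 3, 6, 5, 0; a fifth service missing). Imputed count = (3 + 6 + 5 + 0)/4 = 14/4 = 3.5 contacts, whatever the fifth service is. The imputed count exceeds zero whenever any completed count does, so such a participant is counted as a user of a service for which no answer was given. That affects both the proportion of users and the quantity used.

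**4. MINI** (assumed: yes/no items coded 1/0). With five completed items there are 2^5 = 32 patterns. Only all-yes and all-no give a mean of 1 or 0, so 30/32 = 93.8% yield a fraction that is neither answer. If the mean is taken over the whole measure, it also mixes answers about three different conditions.

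**5. Reach of the error.** The feasibility criteria are app engagement, retention, and record availability or MINI completion. None uses an imputed item value.

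**The case against.** The case for leaving this alone has several parts.

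- **The rule names no instrument.** This is correct: the scope is inferred from general wording and the lack of an exemption. The authors may have had only scales in mind, but the text does not say so.
- **The rule is conditional.** The bracketed condition limits how often it applies, and its threshold may properly sit in the full protocol or SAP. It does not cure the mismatch: an EQ-5D-5L with four of five answers could well pass, and the same difficulty arises.
- **EQ-5D-5L has its own sentence.** The reference to NICE could be read as a separate procedure. It speaks to how utilities are estimated and does not say that missing dimensions are handled differently, so the question stays open.
- **An unscoreable profile yields no utility, not a false one.** This is fair for the fractional cases, and likewise for a fractional MINI item. The analyst must then round, interpolate or set the value to missing, with no instruction. It does not cover the whole-level cases or the service counts, where the rule returns a usable but unfounded value.
- **Little depends on it.** This largely stands. The summaries are tertiary, there are no between-arm tests, missingness is reported separately for each measure, and a researcher enters responses during remote interviews, so isolated gaps should be uncommon.

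**Conclusion.** The point holds as a minor to moderate defect. It is a stated rule that is wrong for part of what it covers, not a detail left to another document. It affects utilities, QALYs, service users and quantities, cost drivers and MINI summaries, all descriptive. How often is unknown, since the article gives no item non-response rate; it is probably seldom. The percentages in the working depend on the assumed item structures and independence, and they apply only to questionnaires that already have a gap.

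Three stronger readings are not supported:

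- A reader might infer that the feasibility decision is compromised. It is not, because none of its criteria uses imputed scores.
- A reader might put a sum in pounds on the resource-use error. The plan states no unit costs and no cost per participant, and the questionnaire's items are not shown, so any such sum would be invented.
- A reader might say that the protocol expressly applies the rule to these three instruments, or that invalid diagnoses will follow. The first is an inference from scope. The second is not established, since a fractional answer cannot be entered into a diagnostic algorithm at all.

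The sample size and its stated precision are unaffected.

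**What to change.** Replace the single rule with a few sentences:

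- Use person-mean substitution only for PHQ-9, GAD-7 and the Postpartum Bonding Questionnaire, within subscale, with a stated minimum of completed items.
- Set the EQ-5D-5L utility to missing if any dimension is missing.
- Leave missing resource-use items missing, and report each service with its own denominator.
- Class a MINI module as missing unless its algorithm resolves from the answers given.

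The price is slightly fewer complete utilities (and hence QALYs) and service-use records. Trial conduct, sample size and feasibility criteria do not change.

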### Data monitoring and auditing

#### Audit

The study will be subject to the audit and monitoring regime of the Greater Manchester Mental Health NHS Foundation Trust, the University of Manchester, Manchester University NHS Foundation Trust and Mersey and West Lancashire Teaching Hospitals NHS Trust.

#### Independent oversight

Independent oversight will be provided by a Trial Steering Committee (TSC), consisting of an independent chair, a statistician, a clinical academic, a parent representative, and the study Chief Investigator. All TSC members except the Chief Investigator are independent of the study team. The TSC will meet every 9 months to provide advice on the conduct, progress and safety of the research and to ensure that the project is conducted to the rigorous standards set out in the Department of Health’s Research Governance Framework for Health and Social Care [26] and the Guidelines for Good Clinical Practice [41].

#### Harms

A Standard Operating Procedure (SOP) will be followed to ensure that adverse events are monitored and reported throughout the study in line with sponsor policies and local site reporting systems. During this study, information about adverse events may be reported during study assessments, via spontaneous participant report, during safety phone calls (app group only), or may be gathered from electronic health records. All adverse events will be documented and assessed for seriousness, relatedness, and expectedness. Where needed, additional information will be sought to allow accurate categorisation. All events categorised as serious (Serious Adverse Events, SAEs) will be reported to the study sponsor and TSC chair. All adverse events categorised as serious, related to the study procedures, and unexpected (Suspected Unexpected Serious Adverse Reactions, SUSARs) will be reported to the study sponsor, TSC chair and ethics committee within seven calendar days.

### Patient and public involvement (PPI)

Throughout the study lifecycle, we have consulted and involved a diverse group of parents with relevant lived experience. An individual with lived experience of perinatal mental health problems is a co-investigator on the study and is actively involved in managing and delivering the research. We established a study PPI group whose members have varied experiences of parenting and perinatal mental health, including lived experience of postnatal depression, postpartum psychosis, and coping with stillbirth. The group is ethnically/linguistically diverse and includes Urdu, Cantonese and Arabic speakers, to reflect the languages in which the CareLoop PND app is available. The PPI group have had a significant impact on the study to date: providing detailed feedback on the design of the CareLoop PND digital screening system during a series of co-design workshops, designing and amending participant-facing documents (e.g. participant information sheets, study posters) to improve readability and presentation, filming and editing participant-facing videos, troubleshooting specific aspects of study procedures (e.g. how to maximise recruitment), helping to format documents translated into the minority languages (Arabic, Urdu, Cantonese), and taking part in role plays of study assessments as part of research staff training. The PPI group will continue to meet every 2–3 months during the study to oversee the study from a lived-experience perspective and to advise on emerging issues. Regarding wider stakeholder involvement, health professionals also contributed to the digital screening system design within two co-design workshops.

